#### Longitudinal analyses

Consistent with Consolidated Standards of Reporting Trials (CONSORT) guidelines, data on recruitment, participation rates, and drop-out will be collected and reported [40]. Should the frequency of missing data be less than 5%, baseline value carried forward will be conducted with proposed analyses. If the missingness becomes prevalent, the differences in demographic characteristics will be assessed between the completers and the noncompleters to identify possible non-differential missing patterns between intervention groups or demographic subgroups. If missing data appears to be not completely at random, a post-stratification method will be employed to address the issue. Otherwise, missingness will be assumed to be completely at random in the subsequent analyses. Since the data generated in this trial is longitudinal in nature, linear mixed models (LMM) or generalized linear mixed models (GLMM) will be applied to assess intervention effects on continuous and discrete outcomes, respectively [41]. A three-level LMM or GLMM (repeated observations, within subjects, within clusters) will be conducted with individual as the unit of analysis and cluster (day) entered as a random intercepts. Intervention indicators, as well as other key demographic confounders, will be included in the models as fixed effects. Subjects within each cluster will be considered independent from each other. For repeated observations within subjects, an unstructured correlation structure will be used. Finally, a separate set of analyses will be performed on participants who provided complete data. Should completer and ITT analyses yield similar results, the most conservative analysis will be reported. Should analyses yield different results, multiple analyses will be reported.

More specifically, the primary hypothesis will be tested using a linear mixed model with group (intervention, control) as a between subjects factor (fixed effect) and time (baseline, 1 month, and 1 year follow-up) as a within subjects factor. Sunbathing is the primary outcome variable. Secondary outcome variables including sun protection behavior, sunburns, and use of sunless tanning products will be examined in the same way. Because these dependent variables appear to be associated with different motivating variables, they are likely to be conceptually distinct and will be analyzed in separate models. Age will be entered as a covariate in both models because these factors are typically associated with the outcome variables [42]. Significant group by time interactions would be consistent with the primary hypothesis, such that the intervention group would engage in higher rates of sun protection and lower rates of sun exposure than the control group at 1- and 1-year follow-up, but not baseline. In exploratory analyses, ethnicity (White, nonwhite), and age will be entered as factors in the original model to determine differential response by these factors.

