### Outcomes and study measures

The primary outcome is sunbathing. Participants will be asked how much time they spent in the sun with the intention of getting a tan in the past month using a 9-point scale where 0 = never, 1 = once, 2 = twice, 3 = once a month, 4 = twice a month, 5 = once a week, 6 = twice a week, 7 = almost every day and 8 = everyday. The wording of this item is based on recommendations made by Glanz and colleagues 2008 [35]. However, the response options will be tailored to one month's time. This measure will be implemented at baseline, which will reflect sunbathing in the month previous to our contact with them at the beach, at 1-month follow-up to reflect sunbathing in the month following our contact with them at the beach, and at 12-months to reflect their sunbathing during one month of the following summer.

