### Intervention

#### Experimental condition

In addition to completing the questionnaires, participants randomized to the experimental condition will receive a brief intervention designed to increase sun protection behaviors, discourage sunbathing, and promote use of sunless tanning products as a substitute for sunbathing. First, participants will pose for three photographs: a standard Polaroid and two Polaroids using the UV filter that illuminates sun damage. Participants will have the opportunity to compare and take home the standard photo and one UV photo. During the development of the photographs, participants will be introduced to two products: sunscreen with SPF 30 and sunless tanning lotion. They will receive instruction on the proper use of each product and will be given a single use sample of each product to keep. The research assistant will guide the participant in applying the sunless tanner on a small portion of skin, so they can observe the skin-coloring effect firsthand. Participants will also be encouraged to use sunscreen on a daily basis, but especially while spending time in the sun. For the sunless tanning products, participants will receive instructions for proper use, be informed of the benefits of sunless tanning compared to sunbathing, be educated about the safety (and limitations, i.e., does not provide sun protection) of the product and its ingredients, and will view female models (research staff) with a sunless tan. Use of sunless tanning lotion will be encouraged as a healthy alternative to sunbathing rather than a supplement to sunbathing. The benefits to health and physical appearance of sunless tanning lotion as an alternative to sun bathing will be strongly emphasized as will the risks of continued sun exposure. Once participants view their photo, they will be instructed to post it in their home where it could serve as a reminder to use these products (e.g., medicine cabinet, near sundries, sports equipment, and refrigerator). Finally, participants in the experimental condition will receive an educational pamphlet that covers information about skin cancer detection, prevention, symptoms, and diagnosis, complete with graphic images of skin cancer lesions. A research assistant will review the main points of the pamphlet with the participant before giving it to the participant to take home.

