### Primary and secondary hypotheses-analysis plan

#### Analytic plan

Intent to treat analyses (ITT) will be used to examine the primary outcome. All participants randomized will be included in analysis and analyzed by original group assignment [38]. Mixed effects regression modeling, implemented via SAS PROC MIXED that incorporated a random intercept trend, will be used since this analytic approach includes all participants that have data available on at least one time point [39]. Missing values will not be imputed or discarded, rather they will be treated as missing in the analysis. The analysis will include the linear time effect, the main effect of condition and the time and condition interaction to examine whether the experimental condition resulted in greater changes in sun behavior than the control condition over time. Age will be included as a covariate in the analysis. Chi-square analyses will be used to examine the differences between two conditions for the use of indoor tanning and sunless tanning at baseline and then at 1-month follow-up. Only participants with complete data at both time points will be included in the chi-square analyses.

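### Similar demographics in completers and non-completers cannot justify assuming data missing completely at random; measured sunbathing belongs in the check, by arm

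*Protocol article*

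**What the plan says.** All of the rule stands in the protocol article, Longitudinal analyses. Below 5% missing data, baseline values are carried forward. If missingness is prevalent, "the differences in demographic characteristics will be assessed between the completers and the noncompleters", with the aim "to identify possible non-differential missing patterns between intervention groups or demographic subgroups". Two branches follow:

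- Where the comparison suggests a departure from missingness completely at random, some form of post-stratification is applied.
- Where it does not, the fallback reads: "Otherwise, missingness will be assumed to be completely at random in the subsequent analyses".

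The same section plans a completer analysis beside the intention-to-treat analysis. If the two are similar, the more conservative is reported; if they differ, several analyses are reported.

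Other sections bear on this:

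- Outcomes and study measures, on sunbathing: "This measure will be implemented at baseline, which will reflect sunbathing in the month previous to our contact with them at the beach". It is measured again at 1 and 12 months.
- Analytic plan: the mixed model is chosen because "this analytic approach includes all participants that have data available on at least one time point". Chi-square tests of indoor and sunless tanning at baseline and 1 month use only women with data at both times.
- Longitudinal analyses, on the model: "For repeated observations within subjects, an unstructured correlation structure will be used".
- Sample size: loss of 15% at 1 month and 25% at 12 months is allowed for.

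**The concern.** The second branch treats the absence of a visible pattern as evidence of missingness completely at random. The only characteristics named in the comparison are demographic. Women of the same age and ethnicity can differ in sunbathing, and response can depend on that difference without disturbing demographic balance.

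Dependence that differs by arm is what would distort the comparison. A mechanism is easy to imagine. In the experimental condition the advantages of sunless tanning are stressed, "as will the risks of continued sun exposure", whereas control women receive a souvenir photograph and unrelated samples. An intervention woman who went on sunbathing might be less willing to report it. The documents do not say that this happens.

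The stated aim also names the wrong kind of pattern: missingness that is *differential* between arms is the kind to look for.

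At stake is whether analyses that rely on the assumption, and readers who take comfort from it, are misled when a quarter of 12-month outcomes may be absent.

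**Working it through.** **1. Inputs and the plan's own figures.** From Sample size and Table 1: SD 2.0, effects 0.75 h (1 month) and 0.70 h (12 months), correlation with baseline 0.50 and 0.45, intra-cluster correlation 0.01, loss 15% and 25%. The formula is n per group = 2·SD²·(1.960+0.842)²/δ² × f × [1+(m−1)·0.01], and total = 2n/(1−d). Here m is women per cluster and d is loss. The factor f is 1−ρ² with one follow-up and (1+ρ)/2−ρ² with two.

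- A: 111.6 × 0.75 × 1.11 = 92.9; total 218.7 (stated 94 and 222).
- B, with the text's ρ = 0.45: 128.1 × 0.7975 × 1.13 = 115.5; total 307.9 (stated 118 and 314).
- C, ρ = 0.50: 60.6 × 1.08 = 65.4; total 174.4 (stated 66 and 176).

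The table is reproduced closely and its dropout inflation is sound. No stated figure depends on the missingness check.

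**2. Simple illustration at 12 months.** Assume 25% of the intervention arm is lost, observed women show 0.70 h, and lost control women resemble observed ones.

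- Every lost intervention woman has no benefit: 0.75 × 0.70 + 0.25 × 0 = 0.525 h. The observed effect is 0.70/0.525 = 1.33 times the effect in all randomised women.
- Half of them have no benefit: 0.70 × (1 − 0.125) = 0.6125 h.

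**3. Which analyses are exposed.** A large-sample simulation used 400,000 women per arm, normal outcomes with SD 2.0, correlations with baseline of 0.50 and 0.45, and a true 12-month effect of −0.70 h. Assumptions not in the documents: a correlation of 0.50 between 1 and 12 months, complete 1-month data, and the dropout odds ratios (OR) per hour per week. Loss was 25% in each arm at 12 months. The likelihood estimate uses baseline and 1-month sunbathing.

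| Dropout depends on | Completers, raw | Completers, change | Completers, ANCOVA | Likelihood |
|---|---|---|---|---|
| Nothing | −0.708 | −0.704 | −0.706 | −0.707 |
| Baseline, both arms, OR 1.5 | −0.708 | −0.703 | −0.706 | −0.707 |
| Baseline, intervention only, OR 1.5 | −0.866 | −0.503 | −0.703 | −0.704 |
| 1-month, intervention only, OR 1.5 | −0.886 | −0.706 | −0.806 | −0.706 |
| Unreported 12-month, intervention only, OR 1.25 | −0.920 | −0.822 | −0.876 | −0.857 |
| Unreported 12-month, intervention only, OR 1.5 | −1.069 | −0.907 | −0.999 | −0.967 |
| Unreported 12-month, both arms, OR 1.5 | −0.704 | −0.702 | −0.703 | −0.705 |

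- Dropout explained by observed sunbathing leaves the likelihood estimate at about −0.70 to −0.71, while completer estimates can move either way (−0.503 to −0.886).
- Arm-specific dropout on the unreported outcome biases every estimator. The likelihood estimate is 0.857/0.70 = 1.22 to 0.967/0.70 = 1.38 times the truth.
- In those two rows completer ANCOVA and likelihood differ by only 0.876 − 0.857 = 0.019 h and 0.999 − 0.967 = 0.032 h. Agreement between the two analyses would not reveal the problem.
- The same dependence in both arms did no harm here, so the check has to be made by condition.

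**The case against.** The strongest reply is that the primary analysis does not need missingness completely at random. Baseline and 1-month sunbathing enter the mixed model as repeated outcomes, so a correctly specified likelihood fit needs only missing at random. This stands. A reader might infer from the second branch that the primary result rests on the stronger assumption; the model described does not require it.

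Other replies stand in part:

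- The comparison also looks for patterns between intervention groups, and completer and intention-to-treat results are set side by side. It is therefore too strong to say that demographics alone decide whether dropout biases the result. Neither safeguard, however, can show dropout driven by an unreported outcome.
- The completer result replaces the intention-to-treat result only when it is similar and the more conservative of the two. That limits the harm, though neither term is defined.
- No post-stratification variables are named. A reader might infer that sunbathing is excluded there; the text does not say so.
- Nothing documents that sunbathing drives dropout. The Retention section describes the same incentives and contact attempts for all women.
- The extended check would not detect dependence on unreported 12-month sunbathing. This is correct, and it is why the fix needs a second element.
- A condensed article may leave sensitivity analyses to a fuller document. True, but the criticism is of a rule that the article does state.

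**Conclusion.** The point holds in a limited form. A demographic comparison with no visible pattern cannot support missingness completely at random, and the outcome measurements best suited to the check are not named in it. The primary mixed model, if correctly specified, largely absorbs dropout explained by observed sunbathing.

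What remains exposed is the completer analysis, the chi-square tests restricted to complete data, post-stratification if confined to demographics, and arm-specific dropout that depends on later unreported sunbathing. Only the last also reaches the primary model.

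A reader might conclude that the trial's effect will be overstated by a third. The documents do not support that. The fall from 0.70 h to 0.525 h assumes no benefit in any lost intervention woman, and becomes 0.6125 h if half of them have none. It also describes a contrast of observed women. If losses accumulate, 25 − 15 = 10 of the 25 percentage points would have 1-month data, and the mixed model could recover part of the gap where lack of benefit already shows by then. The simulated inflation of 22% to 38% likewise depends on assumed odds ratios.

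This is a worthwhile, inexpensive improvement. It does not show that the primary analysis is invalid.

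**What to change.** In Longitudinal analyses:

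1. Compare completers and non-completers, by condition, on baseline sunbathing and, where available, 1-month sunbathing, as well as demographics.
2. Include baseline sunbathing in any post-stratification.
3. Replace the fallback to missing completely at random with missing at random under the mixed model as the working assumption.
4. Add one sensitivity analysis that departs from missing at random, for example giving lost intervention women control-like follow-up values. The extended check cannot detect dropout driven by unobserved outcomes.
5. Change *non-differential* to *differential*.

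The cost is revised wording and a small amount of extra analysis, with no new data collection. The sensitivity estimate may be less favourable than the main one.

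### A result-dependent reporting rule lets the completer analysis replace the ITT mixed model as the only reported primary result; the no-imputation and baseline-carried-forward rules also conflict, with little impact

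*Protocol article*

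**What the plan says.** The Analytic plan section sets the analysis of the primary outcome without condition: "Intent to treat analyses (ITT) will be used to examine the primary outcome". It specifies a mixed effects model that uses every woman with data on at least one occasion, and adds: "Missing values will not be imputed or discarded, rather they will be treated as missing in the analysis".

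The Longitudinal analyses section changes this in two ways.

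- **Reporting.** It adds a completer analysis: "Finally, a separate set of analyses will be performed on participants who provided complete data". The choice between the two follows: "Should completer and ITT analyses yield similar results, the most conservative analysis will be reported". For the other case it says: "Should analyses yield different results, multiple analyses will be reported".
- **Missing data.** For low missingness: "Should the frequency of missing data be less than 5%, baseline value carried forward will be conducted with proposed analyses". If missingness is prevalent, completers and noncompleters are first compared on demographics. Then: "If missing data appears to be not completely at random, a post-stratification method will be employed to address the issue". Only if that is not needed: "Otherwise, missingness will be assumed to be completely at random in the subsequent analyses".

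The end of the same section names a linear mixed model for the primary hypothesis. The Sample size section allows for losses of 15% at 1 month and 25% at 12 months. The abstract gives 250 women.

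**The concern.** The analysis that answers the primary question should be fixed before the results are known. Under the reporting rule, the ITT result appears alone, the completer result appears alone, or both appear, depending on how the two compare. When they are judged similar and the completer result is judged the more conservative, a selected subgroup's result stands in the report where the plan promised ITT. The reader then cannot recover the ITT estimate and its interval.

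The missing-data wording raises a second, smaller problem. An unconditional statement that nothing is imputed cannot stand beside a rule that imputes baseline values below a threshold. Carrying baseline forward treats each missing woman as unchanged, so it shrinks the estimated effect.

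**Working it through.** **1. Can the completer result displace ITT?** Set the sentences side by side.

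| Situation | Analytic plan | Longitudinal analyses |
|---|---|---|
| Results similar | ITT | only the more conservative of ITT and completer |
| Results different | ITT | both reported |

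In the first row the two sections give different answers whenever the completer result is the more conservative one. The choice needs both results in hand.

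**2. Whom does the completer set leave out?** Inputs from the Sample size section and abstract: loss of 0.15 at 1 month and 0.25 at 12 months, N = 250. Table 1 applies these rates by time point: 2 × 94 / 0.85 = 221.2 (printed 222) for the short-term scenario, and 2 × 118 / 0.75 = 314.7 (printed 314) for the 12-month scenario. Assume that complete data means all three time points. The excluded share then depends on how far the two losses overlap:

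- all women lost at 1 month are also lost at 12 months: 0.25, or 62.5 of 250
- independent losses: 1 − 0.85 × 0.75 = 0.3625, or 90.6 of 250
- no overlap: 0.15 + 0.25 = 0.40, or 100 of 250

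So 25% is the floor, and the range is 25% to 40%.

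**3. How far could the choice move the estimate?** This is illustrative. Assume equal arms, random loss, no clustering, SD 2.0, within-subject correlation 0.50, and a baseline-adjusted 12-month comparison as a stand-in for the mixed model. Assume also that conservative means the smaller benefit and that every pair of results is judged similar.

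- Residual variance: 4 × (1 − 0.50²) = 3.
- Available-data estimate: 250 × 0.75 / 2 = 93.75 per arm, variance 3 × 2 / 93.75 = 0.0640.
- Completer estimate, independent losses: 250 × 0.6375 / 2 = 79.7 per arm, variance 3 × 2 / 79.7 = 0.0753.
- Completers are a subset, so the variance of the difference is 0.0753 − 0.0640 = 0.0113 and its SD is 0.106.
- The mean of the smaller of two such estimates lies SD / √(2π) = 0.106 / 2.507 = 0.042 hours below the common mean.

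That is 0.042 / 0.70 = 6% of the assumed 12-month difference. With no overlap the completer arm is 75, its variance 0.0800, the SD of the difference √0.0160 = 0.126 and the pull 0.050. With full overlap the two estimates coincide in this simplified comparison and the pull is 0. If dropout is related to sunbathing the gap could be larger, and the documents give nothing to size it.

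**4. Type I error.** An illustrative simulation under the same assumptions (4,000 trials with no effect, independent losses) gave rejection rates of 4.7% for the available-data analysis and 4.9% for completers. Requiring significance in both, one reading of most conservative, gave 3.0%.

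**5. Would the under-5% rule ever apply?** Under 5% of 250 means at most 12 women missing. The binomial probability of 12 or fewer is about 3 × 10⁻⁷ at 15% loss and about 1 × 10⁻¹⁷ at 25%. If it did apply, the shrinkage is at most about 0.05 × 0.70 = 0.035 hours.

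**The case against.** The strongest defence is that the rule leans against the investigators. Read as reporting the less favourable result, it cannot raise the false-positive rate. It also acts alone only when the two results are close, and both are shown when they are not. All of this stands and limits the severity. It does not answer the point, because the choice still rests on seen results and can remove the ITT estimate from the report.

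Definitions of similar and conservative may sit in a statistical analysis plan that is not shown, so their absence from an article is not counted here. The objection is to the stated rule, which would remain result-dependent with any definitions.

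On imputation, the baseline rule may be meant as an added analysis. The text does not say so, but the reading is possible and the branch is nearly unreachable.

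Three stronger readings are tempting and not supported:

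- **A reader might infer that the trial has no defined primary answer when the analyses differ.** The Analytic plan names ITT without condition, and the Longitudinal analyses section names a linear mixed model for the primary hypothesis. Reporting both leaves that intact.
- **A reader might infer that power falls below the planned figure.** In the simulation at a true difference of 0.70, the available-data analysis rejected in 77% of trials and both analyses in 68%. That gap counts every trial significant in only one analysis as a failure. The plan may treat those as different and report both. If similar means the same significance verdict, the choice changes no verdict.
- **A reader might infer that the plan simply assumes data missing completely at random.** A demographic comparison and post-stratification come first. Stating that stronger assumption does not alter the estimate from a likelihood-based model on all available data.

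**Conclusion.** The concern holds in limited form and should be corrected. The reporting rule contradicts the unconditional ITT statement and can put a subgroup lacking 25% to 40% of the women in place of ITT as the only reported result. That range assumes the planned losses and that completers need all three time points. On the less-favourable reading, the consequence is a reported estimate pulled toward the smaller of the two, of the order of 0.04 hours per week (0 to 0.05 across the overlap cases) under random loss. It is not an inflated type I error.

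The conflict between no imputation and baseline carried forward is real on the wording but of low impact, given the planned 15% and 25% losses.

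**What to change.** In the Longitudinal analyses section:

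1. State that the ITT mixed model on all available data, under missing at random, is the primary analysis and is always reported as such, whatever the results.
2. State that the completer analysis is a sensitivity analysis and is always reported alongside.
3. Delete the sentence that selects the most conservative analysis.
4. Delete baseline carried forward, or label it a sensitivity analysis, so that it agrees with the Analytic plan.

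The post-stratification step need not be replaced for this purpose. The cost is wording only: no new data, no change in conduct and no change in sample size.

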**Methods and Design:**

This cluster randomized trial will examine whether a beach-based intervention that promotes sunless tanning as a substitute for sunbathing and includes sun damage imaging and sun safety recommendations is superior to a questionnaire only control group in reducing sunbathing frequency. Female beach visitors (N = 250) will be recruited from 2 public beaches in eastern Massachusetts. Beach site will be the unit of randomization. Follow-up assessment will occur at the end of the summer (1-month following intervention) and 1 year later. The primary outcome is average sunbathing time per week. The study was designed to provide 90% power for detecting a difference of .70 hours between conditions (standard deviation of 2.0) at 1-year with an intra-cluster correlation coefficient of 0.01 and assuming a 25% rate of loss to follow-up. Secondary outcomes include frequency of sunburns, use of sunless tanning products, and sun protection behavior.

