### Research goals

In the present study, the efficacy of a multi-component beach-based intervention that features sunless tanning among female beach visitors will be tested. The intervention will promote sunless tanning as a substitute for sunbathing and include sun damage imaging and sun safety recommendations. The primary outcome will be sunbathing at 1-, and 12-months follow-up and a questionnaire-only control group will be employed for comparison. Secondary outcomes will include frequency of sunburns, use of sunless tanning products, and sun protection behavior.

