### Sample size considerations and statistical analyses

#### Sample size

The two-arm cluster randomized trial is designed to have at least 80% power at a 5% significance level to test the hypothesized intervention effects at 1- and 12-months on the primary outcome: average time spent sunbathing per week. Means and standard deviations from our previous investigation were used for sample size estimate. With the proposed analytic method, we estimated the required sample sizes for three testing scenarios, i.e., changes between baseline and 1 month, changes between baseline and 12 months, and the joint test involving all three time points (see Table 1). Sample sizes were calculated using the method developed by Frison [36]. Given the possibility that individuals recruited in the same day may show correlation between each other (intra-cluster correlation or ICC), we adjusted the sample sizes with assumed intra-cluster correlation coefficient of 0.01 with method of Garrett [37]. We anticipate a relatively low level of dependency should it exist (ρ = .01) given that individuals at the beach on one day may not be strongly different from individuals visiting the same location the next day. The estimated minimum sample sizes are presented in the Table 1 with the assumed parameters, specifically, the expected mean difference between the two arms after intervention is assumed to be 0.75 and 0.70 hours sunbathing per week at 1 and 12 months, the within-subject correlation is assumed to be 0.50 at 1 month and 0.45 at 12 months. These estimates allow for withdrawal and loss to follow up of 15% and 25% at 1 and 12 months.

**Table 1 T1:** Sample size for three test scenarios for primary outcome: hours spent sunbathing per week

	Mean (SD)									
									
Test Scenarios	Control	Post-Intervention	Expected difference in mean	Within-subject correlation	No. of cluster (day)	Subject/cluster	Intra-cluster correlation	Minimum size/group	Dropout rate	Adjusted minimum total size
A (0–2 month)	2.10 (2.0)	1.35 (2.0)	0.75	0.50	16	12	0.01	94	0.15	**222**
B (0–12 month)	2.10 (2.0)	1.40 (2.0)	0.70	0.50	16	14	0.01	118	0.25	**314**
C (0–2–12 month)	2.10 (2.0)	1.38 (2.0)	0.72	0.50	16	9	0.01	66	0.25	**176**

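### A significant group-by-time interaction over three time points is read as support for benefit at both 1 month and 1 year, but it cannot show when, or in which direction, the arms differ

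*Protocol article*

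**What the plan says.** All references are to the protocol article.

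- **Longitudinal analyses** gives the most specific statement of the primary test: a linear mixed model with group as the between-subjects factor and time (baseline, 1 month, 1 year) as the within-subjects factor. Its only interpretive statement is that "Significant group by time interactions would be consistent with the primary hypothesis", and the pattern attached is "lower rates of sun exposure than the control group at 1- and 1-year follow-up, but not baseline".
- **Analytic plan** describes the model differently, with a linear time effect, a condition effect and their interaction.
- Neither section names a between-arm contrast at 1 month or at 12 months.
- Three places bear on which time point is primary. **Research goals**: "The primary outcome will be sunbathing at 1-, and 12-months follow-up". **Abstract, Methods and Design**: the study was "designed to provide 90% power for detecting a difference of .70 hours between conditions (standard deviation of 2.0) at 1-year". **Sample size**: "we estimated the required sample sizes for three testing scenarios", namely change to 1 month, change to 12 months, and a joint test. That section has a single 5% level and does not rank the three.

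**The concern.** Two arms and three time levels give an interaction with (2−1)×(3−1) = 2 degrees of freedom. Its null hypothesis is that the between-arm difference is the same at all three times. Rejecting it says only that the difference changed somewhere. Benefit at 1 month only, benefit at 12 months only, and harm can all produce a significant result. The text nevertheless links significance to one particular pattern, lower exposure at both follow-ups.

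What is at stake is the 1-year conclusion. The intervention is a single beach contact, and the abstract states power at 1 year. An effect that fades is an obvious possibility, and the stated test does not separate it from one that lasts. This is not detail that could be left to an analysis plan: the article fixes both the test and its reading, and the reading does not follow from the test.

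**Working it through.** **1. Reproducing Table 1.** Frison–Pocock ANCOVA form, two-sided 5% (sidedness is not stated; this choice reproduces the table) and 80% power, so (1.960 + 0.842)² = 7.849:

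n per arm = 2·SD²·[(1+(r−1)ρ)/r − ρ²]·7.849/δ², rounded up, multiplied by 1+(m−1)·0.01, rounded up, then doubled and divided by (1 − dropout).

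- A (δ 0.75, ρ 0.50, r = 1, m = 12): 83.7 → 84; ×1.11 → 94; 188/0.85 → 222. Exact.
- B (δ 0.70, ρ 0.45 as in the text, r = 1, m = 14): 102.2 → 103; ×1.13 → 117; 234/0.75 = 312. The table prints 118 and 314. The table's own ρ of 0.50 would give 110 and 294.
- C (δ 0.72, ρ 0.50, r = 2, m = 9): 60.6 → 61; ×1.08 → 66; 132/0.75 = 176. Exact.

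Row C reproduces as a 1-df comparison of the mean of two follow-ups, so the table does not size the 2-df interaction. Rows A and B are time-specific tests.

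**2. Inputs for the interaction.**

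- From the article: N = 250, SD 2.0, losses 15% and 25%, correlation with baseline 0.50 (1 month) and 0.45 (12 months), planned effects 0.75 h and 0.70 h.
- Assumed: 125 per arm, hence 106.25 and 93.75 followed; losses nested; 1-to-12-month correlation 0.45–0.60; design effect 1.0 to 1.11, where 1.11 = 1 + 11×0.01.

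**3. Worked case** (1-to-12-month correlation 0.50, design effect 1). For the two between-arm differences in change from baseline:

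- V11 = 4·SD²·(1−0.50)/106.25 = 8/106.25 = 0.0753
- V22 = 4·SD²·(1−0.45)/93.75 = 8.8/93.75 = 0.0939
- C = 2·SD²·(1+0.50−0.50−0.45)/106.25 = 4.4/106.25 = 0.0414

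For a true effect of 0.75 h at 1 month and zero at 12 months, the noncentrality is 0.75²·V22/(V11·V22 − C²) = 9.86. A 2-df chi-square at 5% then rejects with probability 81%. With both planned effects (0.75, 0.70) the noncentrality is 8.63 and the probability is 75%. In this case the test rejects at least as often for the vanished effect as for the hypothesised one.

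**4. Range over the assumptions.** The first column uses observed changes as in step 3. The second uses a mixed model with all available records and unconstrained baseline means.

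| True effect (1 month, 12 months) | Observed changes | Mixed model |
|---|---|---|
| 0.75 h, 0 | 74–86% | 75–88% |
| 0.50 h, 0 | 39–51% | 40–52% |
| 0.40 h, 0 | 26–34% | 27–35% |
| 0.75 h, 0.70 h | 68–77% | 71–79% |

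In the first three rows a 12-month contrast tested at two-sided 5% rejects in 5%, half of that (2.5%) in favour of the intervention.

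**5. Linear time instead.** For the vanished 0.75 h effect, with 93.75 complete cases per arm and correlation 0.50:

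- Times coded 0, 1, 12: the mean is 4.33 and the sum of squares 88.67. The slope difference is (−3.33)(−0.75)/88.67 = +0.0282, with standard error √(4/(93.75×88.67)) = 0.0219. The two-sided rejection rate is about 25%, nearly all in the direction of benefit shrinking (below 0.1% favouring the intervention).
- Times coded 0, 1, 2: the slope is half the 12-month change in complete cases, so rejection is 5%.

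The article does not say which coding applies. With months, the 1-month result enters the slope with the opposite sign to the 12-month result, so the slope does not isolate the 12-month effect.

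**The case against.** **The wording is softer than a decision rule.** The text says that significance would be consistent with the hypothesis and describes a pattern of means. Arms that were equal at 12 months would visibly not show that pattern. A reader might infer that an effect gone by 1 year would usually be declared a 1-year effect. The article does not say so, and the percentages above are not the probability of that claim. This stands. It does not rescue the test, because no other criterion for the primary hypothesis is given.

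**The 2 df are derived, not stated.** Under the linear time effect in the Analytic plan section the interaction has 1 df and the 74–88% does not apply. This also stands, and it exposes a contradiction between two adjoining sections. The Longitudinal analyses text presents itself as the more specific of the two, but both cannot be run as the primary model.

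**High rejection depends on the 1-month effect.** At 0.50 h it is roughly even odds and at 0.40 h about one in three. True, but 0.75 h is the article's own planning value, and all these figures are far above 5%.

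**Time-specific tests were contemplated.** The Sample size section sizes them. That shows intent, but the analysis sections do not carry them forward.

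**Multiplicity.** A reader might also infer that three tests, each at 5%, inflate the error rate. If either the 1-month or the 12-month test alone sufficed, the family-wise rate would be 8.8–9.2%, and 9.8–10.0% with the joint test added. But the three scenarios are listed for sizing, nothing says that any one suffices, and requiring benefit at both times would cause no inflation. The point holds only conditionally.

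**Conclusion.** The concern holds in limited form. The stated test cannot support the stated reading, and the two analysis sections disagree on how time enters the model. At the planning values an effect absent at 12 months gives a significant interaction about three times in four or more (74–88%), against 5% for a 12-month contrast. The figure falls to 39–52% for a 0.50 h effect and 26–35% for 0.40 h. It rests on categorical time, N = 250 split equally, nested losses, an assumed 1-to-12-month correlation of 0.45–0.60 and a design effect of at most 1.11. It measures how poorly the interaction discriminates. It does not show that false 1-year claims would be made at that rate, nor that the 5% level is exceeded. The primary time point also needs settling, since the abstract, Research goals and Sample size sections do not give one consistent answer.

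**What to change.** 1. Model time as categorical in both the Analytic plan and Longitudinal analyses sections.
2. Estimate the between-arm contrast in change from baseline at 1 month and at 12 months, as the Sample size section already contemplates.
3. Claim benefit at a time point only if its own contrast is significant in favour of the intervention. Delete the reading of the interaction itself as an effect at both times.
4. State one confirmatory rule, and align the abstract, Research goals and Sample size sections with it. Either name a single primary time point and test it at 5% with no gate, or keep both time points in a closed test: the 2-df interaction at 5%, then each contrast at 5%.

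The cost is wording and two contrast statements. A 1-month-only result could no longer support a 1-year claim. The gate has a price. At N = 250 with the planned effects, 12-month power in the mixed model is about 62–67% without it and 57–63% with it, a loss of about 4–5 points (400,000 simulated draws per setting). If 12 months alone is primary, the gate brings no benefit. Under the closed test, false 12-month claims in favour of the intervention, when the effect has vanished, occur about 2.5% of the time.
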